#### Concealment mechanism {16b}

The allocation sequence will be concealed from the researcher assessing participants in sequentially numbered opaque, sealed, and stapled envelopes. The envelopes will be kept in a locked drawer.

#### Implementation {16c}

All patients who give consent for participation and who fulfill the inclusion criteria will be assigned to the intervention group or control group through a 1: 1 allocation, according to computer-generated randomization, using blocks of sizes 4 and 6. A Master’s student not involved in participant assessment will prepare the sequence generation and envelopes. The study coordinator will open the envelopes only after the enrolled participant completes all baseline assessments. The estimated time between baseline assessments and allocation will not exceed 5 days. The envelopes will identify the physiotherapist to perform the intervention and which intervention the participant has been assigned to.

### Assignment of interventions: blinding

#### Who will be blinded {17a}

All clinical assessments will be conducted by an evaluator blinded to treatment allocation. In order to reduce blindness bias, participants will be instructed not to disclose any information about the treatment received during reassessment. In the event of unblinding of the assessor, its occurrence and the reason for it will be recorded and reported along with the trial results.

The two physical therapists who will coordinate the treatments will not be blinded to the group allocation, since both professionals will implement the two protocols. The statistician involved in the analysis will be blinded to the group allocation.

Participants will be blinded to the study hypothesis and their group allocation, but rather advised of the overall aspects involved in the treatment of both groups. They will not be informed of the specific treatments applied to each group or of the intergroup differences.

#### Procedure for unblinding if needed {17b}

Not applicable

### Data collection and management {18a}

#### Baseline assessment

This will consist of an evaluation form, questionnaires, and physical assessment. The assessments are summarized in Table 2 and separated according to the domains of the International Classification of Functioning, Disability and Health (ICF).

**Table 2 Tab2:** Assessment according to CIF domains

Functionality and disability	
Body structures and functions	Activity and participation
Pain	AUSCAN
Grip strength	COPM
Pinch strength	NHPT
Muscle activation	BULFT

The evaluation form will characterize the participants’ personal information, such as age, sex, schooling level, occupation, dominant upper limb, anthropometric data (weight, height, body mass index), and demographic data. This form will also include questions related to the clinical history of the participants (e.g., time since diagnosis (in years), use of continuous medications, and orthosis). Participants will also be asked to report their pain level at four different times: average pain over the past 30 days, average pain in the 48 h prior to baseline assessment, and pain at the moment and during the execution of the lateral pinch.

##### Questionnaires

All participants will complete the AUSCAN, a self-reported questionnaire, specific to hand OA, and valid for assessing pain and/or disability in patients with CMC OA [31, 32].

The COPM, used to assess social participation, is characterized as an individualized measure since each participant scores which activities, he/she finds most difficult to perform. The tool encompasses three areas of occupational performance: self-care, productive, and leisure activities. Participants will rate the activities in order of importance on a scale of 1–10, with 1 being minor and 10 very important. Next, the five main occupational performance problems will be scored again, on a scale of 1–10, indicating patient performance in the task and their degree of satisfaction with their execution [33, 34].

##### Physical assessment

All participants will be assessed for manual dexterity, hand function, grip and pinch strength, and muscle activation.

Manual dexterity will be evaluated using the NHPT, a wooden board with nine holes (3 rows × 3 columns) that must be filled with nine wooden pegs. The participant will be instructed to place the pegs into the holes one at a time in any order and then remove them and place them in the container next to the board. The test will be timed [35] and performed bilaterally, starting with the dominant upper limb.

Hand function will be assessed using the activities in the BULFT, which involves performing thirteen tasks. The positioning of the participant and the evaluator’s instructions on executing each task will be in line with the test administration manual. All tasks performed will be timed.

Maximum grip and pinch (pulp-pulp, lateral, and tripod) strength will be determined with a manual hydraulic dynamometer (Lafayette Professional Hand Dynamometer) and Lafayette hydraulic pinch gauge, respectively. The recommendations of the American Society of Hand Therapists (ASHT) will be followed and participants will perform three repetitions of 6 s each, with 1-min rest intervals [36]. The average of the three repetitions will be used for statistical analysis. The tests will be performed bilaterally, starting with the dominant upper limb.

The magnitude of muscle activation will be measured during the grip and pinch strength tests, using a Trigno Wireless System (Delsys Inc., Boston, USA) at a sampling frequency of 1200 Hz and three Trigno mini wireless sensors (Trigno EMG sensor, Delsys Inc., Boston, MA), with a rejection rate higher than 80 dB. To evaluate the thumb APB, the mini electrode will be placed in the center of the thenar eminence, in the same direction as the thumb. For 1st DI assessment, the mini electrode will be placed on the dorsal surface of the hand, in the space between the index finger and thumb, while the participant performs the pinch movement. To evaluate EPB and APL, the mini electrode will be placed in the dorsal region of the forearm above the wrist and on the same side as the thumb, while the participant abducts the thumb [37]. Before positioning the electrodes, the skin in the area will be prepared as recommended by Surface Electromyography for the Non-Invasive Assessment of Muscles (SENIAM) [38].

#### Four-week assessment

After 4 weeks of intervention (13 sessions), a clinical reassessment will be performed by applying the AUSCAN questionnaire, the COPM tool, NHPT, and VAS for the average pain felt in the last 3 days, pain at that time, and pain during the execution of the lateral pinch movement.

#### Six-week assessment

At the end of the treatment (18 sessions), a second clinical reassessment will be conducted within 3 days of the last day of the intervention, repeating all the procedures described in the baseline assessment.

#### Eighteen-week assessment

The follow-up will be performed 18 weeks after the beginning of treatment, that is, 3 months after completion, when participants will undergo the same process described for baseline assessment.

### Plans to promote participant retention and complete follow-up {18b}

Participants will receive information about the study design and the importance of completing the final follow-up. The blind evaluator will contact the participants by telephone approximately 3 days before the scheduled date to arrange the best time and date for the final evaluation to be carried out. In addition, the physiotherapist who was responsible for administering the treatment will call the participants 15 days before the end date of the follow-up requesting them to report the mean pain over the last 15 days according to the VAS (0–100 mm).

### Data management {19}

The data are currently being collected in paper form and stored in binders in an allocated cabinet in the Physiotherapy Department of Federal University of São Carlos (UFSCar). After collection, all forms will be checked for data quality and missing information and then stored in a locked cabinet accessible only by the principal investigator. The data will be entered into the Excel 2011 software by the lead researcher. The database and electronic analyses will be stored on a secure computer server with personal login access authorized by the principal investigator, who will have access to the complete data set (blinded for group allocation), with the co-investigators granted access when necessary. After completion of the study, all data and study documents will be archived by the principal investigator and stored for 5 years in the Physiotherapy Department, in Federal University of São Carlos (UFSCar).

The data is not public and is in the possession of the main researcher, and if requested, it will be made available.

### Confidentiality {27}

The data will be treated anonymously and confidentially and at no time will the full name of the participants be disclosed at any stage of the study.

### Plans for collection, laboratory evaluation, and storage of biological specimens for genetic or molecular analysis in this trial/future use {33}

Not applicable.

## Statistical methods

### Statistical methods for primary and secondary outcomes {20a}

Data will be analyzed according to the intention-to-treat principle. All trial outcomes will be blinded for treatment allocation, and all participants will be analyzed in the treatment group to which they were originally randomized. Statistical analysis will be performed using the Statistical Package for the Social Sciences, version 19.0 (SPSS Inc., Chicago, IL, USA). A 5% significance level will be adopted for all analyses. The normality of the residues will be verified by the Shapiro-Wilk test. Pain, function, activity and participation, grip and pinch strength, dexterity, and muscle activation will be compared between the groups (control and intervention) and stages (pretreatment, 4- and 6-week assessments, follow-up), and interactions between them analyzed by mixed model ANOVA considering group and time factors for repeated measures if the residuals exhibit normality with post hoc contrasts (treated versus control group).

The first statistical procedure will be to verify, in general and at each assessment stage (pretreatment, 13th and 18th assessment, follow-up) if pain, function, activity and participation, grip and pinch strength, dexterity, and muscle activation differ between the intervention and control groups. The second statistical procedure aims to verify whether pain, function, activity and participation, grip and pinch strength, dexterity, and muscle activation change over the four assessment stages (pretreatment, 4- and 6-week assessments, follow-up) within each group.

The quantitative variables will be expressed as minimum and maximum values, means, medians, standard deviations, coefficients of variation, and asymmetry coefficients. Categorical variables will be expressed as frequencies and percentages.

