**Methods:**

This is a randomized, controlled, double-blind, and parallel clinical trial that will include 56 participants, over 40 years old, with radiographic evidence of thumb base osteoarthritis. Participants will be randomly allocated into two groups: control and intervention. The following evaluations will be conducted: the Australian/Canadian Hand Osteoarthritis Index, Canadian Occupational Performance Measure, Nine-Hole Peg Test, grip and pinch strength associated with muscle activation assessment, and Bilateral Upper Limb Function Test at four different times: baseline, session 13, session 18, and follow-up. Treatment will take place over 6 weeks, with reassessments in the fourth and sixth weeks and 3 months after the end of the intervention (follow-up). Qualitative variables will be expressed as frequency and percentage, and quantitative variables as mean and standard deviation. Intergroup comparison of the intervention will be performed by repeated measures ANOVA, considering the effect of the two groups and four assessments, and interactions between them.

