### Sample size {14}

A priori sample calculation was performed in the Gpower 3.1.5 software, considering the comparison of two independent groups (control and intervention) in four distinct stages (pretreatment, 13th and 18th assessment, and follow-up). The statistical test that will be applied was also taken into account, that is, repeated measures analysis of variance (ANOVA) for the variables of interest (pain, manual dexterity, function, strength, and muscle activation). It was considered an effect size of 0.25, 5% significance, and power of 90%, resulting in 46 participants (23 per group). Considering possible sample losses, we will evaluate 20% more, that is, 56 subjects divided into two groups of 28 each.

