### Methods for additional analyses (e.g., subgroup analyses) {20b}

No additional analysis will be performed.

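### The group-by-time model is made conditional on a Shapiro-Wilk result, although the Abstract and the sample size section name it as the test without any condition

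*Protocol article*

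**What the plan says.** Three sections of the protocol article describe the main analysis.

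- **Statistical methods for primary and secondary outcomes {20a}.** "The normality of the residues will be verified by the Shapiro-Wilk test". Group, time and their interaction are then to be analysed by a mixed-model ANOVA, but only "if the residuals exhibit normality with post hoc contrasts (treated versus control group"). The same section states that "A 5% significance level will be adopted for all analyses". It describes no analysis for an outcome whose residuals are judged non-normal.
- **Abstract, Methods.** "Intergroup comparison of the intervention will be performed by repeated measures ANOVA, considering the effect of the two groups and four assessments, and interactions between" these two factors. No condition is attached.
- **Sample size {14}.** "The statistical test that will be applied was also taken into account, that is, repeated measures analysis of variance (ANOVA"). No condition is attached here either, and the calculation follows from this choice: "It was considered an effect size of 0.25, 5% significance, and power of 90%, resulting in 46 participants (23 per group").

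The section on additional analyses {20b} says "No additional analysis will be performed". Its heading concerns subgroup-type analyses, so it neither supplies nor clearly forbids a fallback.

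**The concern.** Under {20a}, the analysis of each outcome depends on a significance test applied to that outcome's own residuals. If the test passes, the outcome gets the group-by-time model and the treated-versus-control contrast. If it fails, the stated rule withdraws both.

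Two things are at stake. First, the primary outcomes (pain at rest and on pinch, AUSCAN function, pinch strength, muscle activation) could be analysed by different methods for reasons unrelated to the clinical question, and some could lose the interaction estimate. Second, an outcome that fails the pretest is no longer analysed by the test on which the trial was sized, which contradicts the unconditional statements elsewhere in the article.

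This is more than a detail left to an analysis plan. Such a plan could name a fallback, but the pretest in {20a} would still choose the method.

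**Working it through.** **Inputs from the article.** Two groups, four stages, effect size f = 0.25, alpha 5%, power 90%, N = 46, raised to 56 ({14}). Shapiro-Wilk on residuals, 5% for all analyses ({20a}; I read the 5% as covering the pretest too).

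**Inputs assumed.** Outcome shapes, and a within-person correlation of 0.5, equal between all pairs of visits before transformation or clipping. The article gives neither.

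**1. The plan's own figure.** For the interaction, lambda = N f² m/(1 − rho). For the between-group effect, lambda = N f² m/(1 + (m − 1) rho). Power comes from the noncentral F.
- Interaction, m = 4, rho = 0.5: N = 30 (lambda = 30 × 0.0625 × 4/0.5 = 15).
- Interaction, m = 4: N = 48 at rho = 0.2 and N = 44 at rho = 0.25.
- Interaction, m = 2, rho = 0.5: N = 46 (lambda = 46 × 0.0625 × 2/0.5 = 11.5).
- Between groups, m = 4: N = 46 at rho = 0 and N = 108 at rho = 0.5.

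So 46 can be reached from the named model, but it cannot be confirmed without the unstated correlation and effect type. The uplift 46 × 1.2 = 55.2 gives 56, as stated. The present point does not turn on this figure; it matters only that the sizing assumes repeated measures ANOVA.

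**2. Does the model need protecting?** I simulated the ungated group-by-time F test under no treatment effect, with 2,000 runs per shape at 23 and at 28 per arm. The shapes were normal, t with 5 df, lognormal with log-SD 0.3, 0.5 and 0.8, and two VAS outcomes clipped to 0–100. Type I error was 4.1% to 5.7% throughout. The Monte Carlo standard error is √(0.05 × 0.95/2000) = 0.5 percentage points, so all values lie within two standard errors of 5%.

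**3. How often would the pretest reject?** The article does not say which residuals are tested. The same runs give:

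| Assumed shape (23 / 28 per arm) | Group-by-visit cell residuals, pooled | Within-subject residuals |
|---|---|---|
| Normal | 9% / 8% | 4% / 4% |
| Lognormal, log-SD 0.3 | 97% / 99% | 49% / 59% |
| Lognormal, log-SD 0.5 | 100% / 100% | 90% / 96% |
| VAS, mean 25, SD 25, clipped | 99.7% / 99.95% | 16% / 20% |
| VAS, means 50, 35, 25, 25, SD 22, clipped | 48% / 61% | 5% / 7% |

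With gamma residuals treated as independent, the rejection rate also depends on how many there are:

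| Residuals tested | Skewness 0.5 | 0.7 | 1.0 |
|---|---|---|---|
| 56 (one per participant) | 24% | 44% | 76% |
| 168 (56 × 3 visits) | 64% | 91% | 99.8% |
| 224 (56 × 4 visits) | 78% | 97% | 100% |

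The 168 row applies to grip, pinch, BULFT and muscle activation, which have no four-week measurement in Table 1 or in the four-week assessment section. For a floored VAS (mean 25, SD 20, n = 56), raw scores were rejected in about 66% of runs and arm-centred values in about 49%. Change scores (assumed means 45 to 25, SD 20, correlation 0.5) were rejected in about 4%, which is close to the nominal rate.

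**4. Does a gated procedure inflate error?** I took one possible gate: a t-test if Shapiro-Wilk passes, Mann-Whitney otherwise, 28 per arm. Over normal, gamma, floored VAS and lognormal data its type I error was 4.9% to 5.3% (10,000 runs each), against 4.9% to 5.2% without the gate.

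**The case against.** The case on the other side has four parts.

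- **A fallback is normally an analysis-plan item, and that plan is not shown.** This stands. A reader might infer that the replacement method will be picked after the data are seen, or that rank tests will be used. The article says neither, and silence about a fallback in a condensed article is not evidence of either. The point is therefore confined to the condition itself.
- **The Abstract and {14} already commit to the model.** They do, so it cannot be said that the planned analysis will certainly be dropped. But the article then states its main analysis in two incompatible ways, and the conditional version is in the section that governs the analysis.
- **Rejection may be rare.** A reader might infer that skewed or floor-limited outcomes will nearly always fail. The test is on residuals, and the primary outcomes are changes from baseline to 6 weeks. Rejection of change scores from a floored VAS was near 4%. The timed tests are secondary. High rates need strong skewness or many pooled residuals. This stands as a limit on size.
- **No inferential error is demonstrated.** Also true: the gated procedure tried above holds its level. The blinding section {17a} adds that the statistician is blinded, which limits favourable selection, although the oversight section {5d} also makes the coordinators responsible for the analysis.

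The objections reduce the size of the concern but do not answer it. The pretest protects nothing that needs protecting, and it can remove the estimate the trial was designed to give.

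**Conclusion.** The concern holds as a badly fixed and internally inconsistent rule. The governing section makes the group-by-time model and its treated-versus-control contrast depend, outcome by outcome, on a Shapiro-Wilk result, while two other sections state the model without condition and one of them sizes the trial on it.

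The consequence is possible inconsistency of method across primary outcomes and loss of the interaction estimate for some of them. The frequency is not known: roughly 5% to nearly 100% per outcome under the assumed shapes, and for the same data it can differ several-fold with the choice of residuals, which the article leaves open.

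The documents and calculations do not support a claim that type I error is inflated. The finding that the ungated model holds about 5% rests on the assumed shapes, complete data and equal correlation between visits before transformation or clipping.

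**What to change.** In {20a}, delete the clause that makes the mixed-model ANOVA conditional on residual normality. State that the same group-by-time model and treated-versus-control contrast will be fitted to every outcome, in line with the Abstract and {14}. Keep residual checks as diagnostics that do not change the main analysis.

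Prespecify one sensitivity analysis (a robust or participant-level bootstrap confidence interval, or a transformed-scale analysis), reported for all outcomes whatever the diagnostics show. Making it depend on how the residuals look would bring back the data-dependent choice. Adjust the sentence in {20b} so that it does not appear to exclude this analysis.

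The cost is a few lines of text and slightly more analysis and reporting. The sample size is unaffected. The change should be recorded before any comparison by group is made.

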### Intervention assignment: allocation

#### Sequence generation {16a}

Individuals who agree to take part in the study and meet all the study criteria will be assigned to the intervention or control group by 1:1 allocation, according to computer-generated randomization, using block sizes of 4 and 6. The two physiotherapists who will apply the interventions will also be randomized in order to avoid bias in blinding.

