### Analysis methods to address protocol non-adherence and statistical methods to handle missing data {20c}

In cases of dropout or withdrawal from the study, the data will be assessed by intention-to-treat analysis. Participants that leave the study without performing the 18 proposed sessions (due to sickness, moving to another town, inability to attend sessions) will be considered protocol deviations.

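### The primary outcomes are week-6 changes, but no week-6 between-group contrast is named as primary, and the planned ANOVA with pretreatment as an outcome stage is less precise than a baseline-adjusted comparison

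*Protocol article*

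**What the plan says.** The Primary outcomes section lists pain at rest and on pinch, AUSCAN function, pinch strength and muscle activation, each as change from baseline to 6 weeks.

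Statistical methods {20a} compares groups and stages, and their interaction, by "mixed model ANOVA considering group and time factors for repeated measures if the residuals exhibit normality with post hoc contrasts (treated versus control group"). Pretreatment is one of the listed stages. Two procedures follow. The first is a group comparison: "The first statistical procedure will be to verify, in general and at each assessment stage (pretreatment, 13th and 18th assessment, follow-up"). The second examines change over the stages separately within each group. No baseline covariate is among the stated factors.

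The abstract describes the same design: "Intergroup comparison of the intervention will be performed by repeated measures ANOVA". Sample size {14} also counts pretreatment as a stage, with two groups compared "in four distinct stages (pretreatment, 13th and 18th assessment, and follow-up").

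On incomplete data, section {20c} says: "In cases of dropout or withdrawal from the study, the data will be assessed by intention-to-treat analysis".

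**The concern.** Neither ordered procedure is a between-group comparison of the week-6 change. The first compares group means overall and at each stage, and the second looks inside each arm, which does not compare treatments. The interaction does compare change between arms, but it pools all stages and is not tied to week 6. The reader is therefore left with several candidate tests of the primary question and no rule for which one decides.

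Two of the planned tests are also poorly aimed. At pretreatment the expected group difference is zero by randomisation, so averaging that stage into an overall comparison dilutes the effect. Testing groups at pretreatment asks about a null hypothesis already known to be true. Finally, baseline is measured for every outcome but the stated model does not use it to reduce the variance of the week-6 comparison. In a trial of 56 that precision is worth having.

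**Working it through.** **Inputs from the protocol article.** Two groups, 1:1; 28 per group enrolled; 5% significance ("A 5% significance level will be adopted for all analyses"); four stages including pretreatment. By Table 1 and the Four-week assessment section, pinch strength and muscle activation are not scheduled at session 13, so they have three stages. (The Secondary outcomes section does list week-4 change for both, and these places should be reconciled. If both were measured then, the four-stage figures apply to them too.)

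**Assumptions, not in the document.** A constant post-baseline difference d = 0.5 SD; unit SD; compound symmetry with correlation ρ from 0.3 to 0.7.

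**The plan's own figure.** "It was considered an effect size of 0.25, 5% significance, and power of 90%, resulting in 46 participants (23 per group"). Taking 0.25 as Cohen's f, a between-groups test over m = 4 stages with ρ = 0 has λ = f²Nm/(1+(m−1)ρ) = 0.0625·46·4/1 = 11.5 on 1 and 44 df, power 0.9125. An interaction test with m = 2 and ρ = 0.5 has λ = f²Nm/(1−ρ) = 0.0625·46·2/0.5 = 11.5 and the same power. With four stages and ρ = 0.5 the required totals are 30 (interaction) and 108 (between groups). So 46 reproduces, but it does not reveal which test was intended. 46 × 1.2 = 55.2, hence 56.

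**Dilution of the overall group test.** Four stages: (0 + d + d + d)/4 = 0.75d. Three stages: (0 + d + d)/3 = 0.67d. The variance of a participant's four-stage mean is (1+3ρ)/4. With effect 0.375 and variance 0.475, 0.625 and 0.775, power is 52%, 41% and 35% at ρ = 0.3, 0.5 and 0.7. For three stages at ρ = 0.5 (effect 0.333, variance 0.667) it is 32%.

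**Week-6 comparison.** Residual variance v is 1 for the raw week-6 mean, 2(1−ρ) for change and 1−ρ² for the baseline-adjusted value. Noncentrality is d/√(2v/28), noncentral t with 54 df (the one df spent on the covariate is ignored). Example at ρ = 0.5: raw 0.5/√(2/28) = 1.87; adjusted 0.5/√(1.5/28) = 2.16.

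**Interaction, four-stage outcomes.** With the same constant effect, λ = (28/2)·d²·(3/4)/(1−ρ), on 3 and 162 df: 3.75, 5.25 and 8.75.

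| ρ | raw week 6 (v) | change (v) | baseline-adjusted (v) | 3-df interaction |
|---|---|---|---|---|
| 0.3 | 45% (1) | 34% (1.40) | 49% (0.91) | 33% |
| 0.5 | 45% (1) | 45% (1.00) | 56% (0.75) | 45% |
| 0.7 | 45% (1) | 66% (0.60) | 73% (0.51) | 69% |

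Adjustment cuts the variance by 9%, 25% and 49% against the raw mean, and by 35%, 25% and 15% against change (for example 1 − 0.91/1.40 = 0.35). It has the highest power of the four in every row.

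**The case against.** The strongest defence is that the plan already contains what is needed. The group-by-time interaction tests whether change from baseline differs between arms, and a week-6-minus-baseline contrast can be drawn from the same model. This stands as far as it goes: the fault is that no such contrast is named, and the global test has less power than the adjusted week-6 contrast in every case tried.

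A reader might infer that the plan estimates the wrong quantity. It does not. Under randomisation the raw week-6 difference and the difference in change have the same expectation, so the loss is of precision. Nor is chance baseline imbalance an extra harm, because it is already part of the variance of the raw contrast.

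A reader might also set the overall test (41% at ρ = 0.5) against a baseline-adjusted mean of the three post-baseline visits (81%) and conclude that power is halved. Neither is the week-6 comparison that the primary outcomes call for. Dilution affects the overall test only, and at ρ = 0.3 that test, at 52%, slightly exceeds the adjusted week-6 contrast at 49%, because it averages over visits.

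A third tempting inference is that participants missing any visit will be dropped. That follows only if classical repeated-measures ANOVA is meant, as the abstract and Sample size {14} suggest. Section {20a} says mixed model ANOVA and commits to intention-to-treat, and a likelihood-based mixed model keeps incomplete cases. The document gives no missingness rate from which to size a loss.

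Finally, covariates and estimation details are often left to an analysis plan. That is fair for details, but section {20a} itself fixes the factors, the stages and the order of the tests, and those choices can be judged. Keeping baseline in the outcome vector is not an error in itself: it is sound if the baseline means are constrained equal.

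**Conclusion.** The point holds as one of targeting and efficiency. The plan names no week-6 between-group contrast as primary, includes an uninformative pretreatment test, and includes an overall test that reduces a constant effect to 75%, or 67% for outcomes with three stages. Its week-6 contrast is valid but gives up precision. Under the stated assumptions baseline adjustment raises power over the raw week-6 mean by 4, 11 and 28 percentage points at ρ = 0.3, 0.5 and 0.7, and over change by 15, 11 and 7 points. The size depends on ρ and d, which the document does not give; at low ρ the gain over the raw mean is small. The ranking of adjusted above raw and change does not depend on d.

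That 46 matches a four-stage between-groups test with zero correlation might suggest that the trial was sized on the diluted overall test. The document does not support that conclusion, since the same number also arises from a two-stage interaction test at ρ = 0.5.

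**What to change.** In Statistical methods {20a}, name as the primary analysis of each primary outcome the between-group difference at 6 weeks, with its 95% CI, from a likelihood-based linear mixed model of the post-baseline values with baseline, visit, baseline-by-visit, group and group-by-visit terms. Include every participant with at least one post-baseline value. A model that keeps baseline as an outcome but constrains its group means to be equal serves the same purpose.

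Drop the group test at pretreatment and the overall group test over stages that include pretreatment. Use one name for the model in the abstract, Sample size {14} and section {20a}, so that it is clear that incomplete cases are retained. A physiotherapist term is optional; section {16a} says "The two physiotherapists who will apply the interventions will also be randomized", but nothing in the document allows its benefit to be sized.

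The cost is wording, plus the notification of changes that the protocol article already foresees. Software, visits and data collection do not change. The change should be made before any comparison by group is seen.
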